#### Body composition

Body weight and body composition will be assessed at all timepoints. Body composition measures include body mass index, waist, and hip circumference (cm), waist/hip ratio, fat mass (kg and %), lean mass (kg and %), and lean mass index (kg/m^2^). Body composition will be measured using bioelectrical impedance (Bodystat 1500, Bodystat Ltd., Isle of Man) following manufacturer’s procedures. Body weight will be measured with a calibrated weight scale.

#### Impact of COPD on daily life

Impact of COPD on daily life will be determined using the CAT [105]. The CAT will only be obtained in the COPD group. The CAT is an eight-item questionnaire that assesses the impact of COPD on self-reported health status and symptoms [105]. Each item is scored from 0 to 5 points where 0 indicates no impact or symptoms, and 5 indicates the worst possible impact or symptoms. Subsequently, scores are summed to a total CAT score of 0–40 points. The CAT takes 3–5 min to complete. The CAT will be measured at baseline, 12 weeks, and at months 6, 9, 12, 15, 18, 21, and the 24-month follow-up.

#### Disease-specific quality of life

For assessment of disease-specific quality of life, the CRQ [106] (SAS version; Self-Administered Standardized) will be used. The CRQ will only be obtained in the COPD group. The CRQ measures the impact of chronic respiratory disease on HRQoL and covers four key domains of HRQoL, including: dyspnoea, fatigue, emotional function, and mastery. Each item is scored on a 7-point Likert scale; scores within each domain are summated for a total score per domain. Research has shown that the CRQ is a valid and responsive test of HRQoL and correlates well with clinical status [107, 108]. The CRQ will be measured at baseline, 12 weeks, and at months 6, 9, 12, 15, 18, 21, and the 24-month follow-up.

#### Health-related quality of life (HRQoL)

Quality of life is assessed with the EQ-5D-5L. It assesses an individual’s HRQoL in five dimensions: mobility, self-care, usual activities, pain/discomfort, and anxiety/depression [109]. Each dimension has five response levels, ranging from level 1 (no problems) to level 5 (extreme problems). By combining one level from each dimension, a health state ranging from 11111 (the best health state) to 55555 (the worst health state) is defined and converted into an index score using a scoring algorithm. The EQ-5D-5L is a valid and responsive measure of HRQoL, also in COPD [110]. The instrument also includes a visual analogue scale, which provides a single global rating of self-perceived health. The scale is scored from 0 (‘the worst…’) to 100 (‘the best health you can imagine’). The EQ-5D-5L takes approximately 5 min to complete.

#### Depression and anxiety

The Hospital Anxiety and Depression Scale (HADS) [111] will be used to assess states of depression and anxiety. The HADS is a reliable 14-item questionnaire regarding feeling of depression (seven items) and anxiety (seven items) in the past 7 days. The items are rated on a 0 (no impairment) to 3 (severe impairment) point severity scale, with a maximum score of 21 for depression and anxiety, respectively. The HADS takes approximately five to ten minutes to complete.

#### Self-perceived change

Self-perceived change in outcomes will be measured via the Global Rate of Change [112] scale with the purpose to quantify the extent to which a participant perceive they have improved or deteriorated over time in the outcome. Participants will provide an answer via a 11-point Likert scale (− 5 = ‘Much worse’; 0 = ‘Unchanged’; 5 = ‘Much better’). The question about self-perceived change will be posed after the following outcome assessments at follow-ups: cardiorespiratory fitness (CPET), anaerobic capacity (BCST), quadriceps power, quadriceps strength, quadriceps endurance, global cognitive function, exercise tolerance (CWRT), 5-STS and SCPT. In addition, they will also rate their perceived change in overall health.

#### Number of responders

Total amount of responders, defined as a response over the known minimal detectable change or minimal important difference for included tests, will be determined and compared between supramaximal HIIT and MICT.

#### Feasibility of interventions

Feasibility of the training programs will be assessed and evaluated between groups using both quantitative and qualitative measurement methods:Completion rate is determined by the total number of participants still performing the exercise training intervention at 12-week and 24-month follow-up. Reasons for non-completion, i.e., dropouts, are also obtained.Attendance rate is determined by the total number of attended sessions divided by total number of sessions prescribed, presented as a percentage. Reasons for non-attendance are also obtained.Adherence to exercise duration is determined as the adherence to the predefined intervals/minutes of the exercise training. Reasons for non-adherence are also obtained.Adherence to exercise intensity is determined as the adherence to the prescribed intensity of the exercise training. Reasons for non-adherence are also obtained. Exercise intensity (absolute workload (W), relative intensity (% of MAP, % of MPO_6_), the level of dyspnoea and leg fatigue (0–10, arbitrary units) on the [47] CR10 scale [47], and perceived exertion (6–20, arbitrary units) on the [47] RPE scale [60]) measured throughout the intervention will be reported. In addition, approximately 5 min after each exercise session, a session RPE [113] will also be collected using the [47] CR10 scale.Attendance rate for resistance training is determined as the self-reported total number of attended sessions divided by total number of sessions prescribed, presented as a percentage.Adherence to resistance training is determined as the self-reported adherence to the predefined number of exercises and number of sets.Exercise fidelity is determined as the incidence of exercise sessions requiring modifications, defined as any deviation from the prescribed exercise such as change in duration, intensity, or cadence.Occurrence and assessment of the severity of adverse events will be documented. Severity of adverse events will be rated into four different categories: (1) minor and temporary, (2) serious symptoms (potential risk of severe injury or life-threatening, (3) manifest injury or disease, and (4) death, as previously described [114]. An adverse event rate will be calculated for each participant as the total number of sessions during which any adverse events occurred divided by the total number of attended sessions.Participant satisfaction with the performed exercise training (supramaximal HIIT / MICT) will be recorded by adaptation of an existing patient satisfaction questionnaire previously used for cycling exercises in COPD [115] (see Tables S3 and S4, additional file 4).

Feasibility will also be determined, in those with COPD, by exploring the participants’ experiences and perceptions of participating in the exercise program by individual face-to-face or telephone interviews after both Phase 1 and Phase 2. A semi-structured interview guide will be used with questions about positive and negative feelings during or after the training, perceptions of participating in the exercise groups, the exercise format (supramaximal HIIT and MICT), perceived effects of the intervention, and if the program was experienced as doable and acceptable. We will also ask about their motivation for doing the intervention and thought about their future exercise. In the interview after phase 2, experiences presented in the first interview will also be followed up.

A sub-sample of up to 15 participants from each group (supramaximal HIIT and MICT) will be included in the interviews after phase 1. Participants with a variation in age, sex, symptoms (baseline CAT), and perceived effects of the intervention will be included for a varied sample. Both those who completed the intervention, and those who interrupted the intervention during either phase 1 or phase 2 will be invited. Everyone who completed an interview after phase 1 will be invited for the interview after phase 2, except for those who interrupted the intervention in phase 1 and did not enter phase 2, would there be any.

Qualitative content analysis [116] will be used for analysis in phase 1, while pattern-oriented longitudinal analysis [117] will be used to longitudinally analyse variations in change over time including both interviews. The COREQ checklist [45] will be used to ensure trustworthiness of the trial.

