#### Home

Participants with COPD that select to continue with endurance training in a home setting will be provided with a cycle ergometer (Smart ZBike, Zycle, Valencia, Spain) for unsupervised supramaximal HIIT or MICT. Alternatively, if a participant would like to continue at home but does not want to receive a cycle ergometer, they can continue with walking-based HIIT or MICT (HIIT-Walk or MICT-Walk). The HIIT-Walk and MICT-Walk build on the same principles as the supramaximal HIIT and MICT exercise performed on a cycle ergometer but are modified to be suitable during walking. See Tables 2 and 3 for details.

**Table 3 Tab3:** Description of Endurance Training (ET) in line with TIDieR and CERT guidelines

Variable	Supramaximal HIIT	MICT	HIIT-Walk	MICT-Walk
1. ET objective	The ET objective for all interventions is to improve peak VO_2_ on a CPET and exercise duration on a CWRT.			
2. Training device / type of exercise	Cycling on a stationary cycle ergometer (Smart Zbike, Zycle, Valencia, Spain)		Outdoor walking	
3. Supervision and delivery	First 12 weeks and outpatient last 21 months: Group of 4-5 individuals under the supervision of a trained instructor^a^, face-to-face delivery / Home or mix last 21 months: unsupervised cycling, individual, phone call delivery every two weeks		Unsupervised walking training, individual, phone call delivery every two weeks	
4. Setting	First 12 weeks: outpatient (local gym or rehab center) / Last 21 months: Home, outpatient (local gym or rehab center) or mix (local gym or rehab center + home)		Home	
5. Adjunct	First 12 weeks: none / Last 21 months: RT (see Table 4)		RT (see Table 4)	
6. Program duration	12 weeks + ≈ 21 months		≈ 21 months	
7. Frequency of sessions	Week 1-6: 2x/week / Week 7-12: 3x/week / Week 15 to 102: 2x/week		Week 15 to 102: 2x/week	
8. Exercise selection	10×6 sec intervals against an individualized intensity with 48 sec recovery^b^ between intervals (20s passive, 28s active) for 10 min	Continuous cycling against an individualized intensity for 20 min	10×10 sec intervals at an individualized maximal walking speed with 50 sec of active rest between intervals for 10 min	Continuous walking at an individualized intensity for 20 min
9. Warm-up / cool-down	5 min at 30% of MAP at 50-70 RPM^c^		5 min at a walking speed at Borg dyspnea <3	

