#### Passive control group: usual care

The passive control group will receive usual care alone and a standardized phone call (see additional file 4) every 3 months including assessment of symptoms of exacerbations. Health status (CAT) and disease-specific quality of life (CRQ) will be assessed by sending a letter with the questionnaires via the post for self-administration or by a phone call. We will match the participants in the usual care group to those randomized to HIIT or MICT by age, sex, disease severity (GOLD A/B/E), educational level, and physical activity.

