**Visit 5**																			
PET/CT^e^							X												X
I**nterventional**																			
Feasibility^c^									X						X				
Adverse events									X						X				
Exacerbations / hospitalisations / mortality									X						X				

Schedule of enrolment, interventions and assessments. The number of weeks can vary slightly depending on schedueling and thus time needed for follow-up assessments (2-3 weeks) and weeks of rest before starting the phase 2 (1-2 weeks). The schedule is representative for participants in Umeå, Sweden, minor differences exist for participants in Hasselt, Belgium, due to logistics

*HIIT* supramaximal high-intensity interval training, *MICT* moderate intensity continuous training, *mMRC* Medical Research Council Dyspnea Scale, *MoCA* the Montreal Cognitive Assessment test, *CPET* cardiopulmonary exercise test, *BCST* Borg cycle strength test, *CAT *COPD assessment test, *CRQ* Chronic Respiratory Disease Questionnaire, *HADS* Hospital Anxiety and Depression Scale, *MNA* Mini-Nutritional Assessment, *PET/CT* positron emission tomography/computed tomography

^a^only mMRC is used for screening

^b^only CAT is used for screening

^c^not for usual care group

^d^not for HC group

^e^only for those enrolled at Umeå, Sweden

^f^(superscripted) MoCA is only performed at baseline at 24-months

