#### Statistical methods—outcomes

For primary and secondary outcomes with continuous data, treatment effect will be estimated by mean change-from-baseline (delta-value (Δ)) with 95% confidence intervals and the effect size (ES). The between-group effects will be analysed using analysis of covariance (ANCOVA). In the ANCOVA, baseline values, age, sex, centre, and VO_2_peak will be used as covariates. In phase 1, the primary analyses will be one model for the COPD group and one model for HC. In addition, to investigate any differential effects to the interventions between COPD and HC, a two-way ANCOVA including the Group (COPD/HC) × Intervention (supramaximal HIIT/MICT) interaction will be performed. In phase 2, there will be one model with the three arms (supramaximal HIIT, MICT, and usual care). Additional details will be provided in the SAP.

The assumptions of linearity, normality of residuals, and homogenous variance will be checked using residual plots, normal quantile plots, and histograms. Violations of linearity and normality assumptions will be dealt with by transformations of the dependent variable or non-linear modelling of the independent variables. Outliers will not be removed unless there is a methodological reason for it.

Feasibility of intervention outcomes and number of responders will be described with descriptive statistics and analysed with between group (HIIT/MICT) comparisons in both the COPD (phase 1 and 2) and HC group (phase 1).

In phase 1, hospitalization and exacerbations during the intervention will be presented descriptively. In phase 2, mortality, hospitalizations, and exacerbations will be presented with descriptive statistics and analysed using Kaplan–Meier curves and Cox proportional hazard models.

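### The one comparative adverse event rate that the article defines is tied to attended sessions, so it misses events between sessions and is distorted by early leaving

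*Protocol article*

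**What the plan says.** In the protocol article, the section Feasibility of interventions lists the adverse event items. The bullet begins broadly: "Occurrence and assessment of the severity of adverse events will be documented", with four severity categories that run up to death. It then sets one number per participant, "the total number of sessions during which any adverse events occurred divided by the total number of attended sessions".

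The section Statistical methods—outcomes says how this list is used: "Feasibility of intervention outcomes and number of responders will be described with descriptive statistics and analysed with between group (HIIT/MICT) comparisons", in the COPD group for both phases and in the healthy controls for phase 1.

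Events that do not depend on sessions appear elsewhere in that section. For the first 12 weeks: "In phase 1, hospitalization and exacerbations during the intervention will be presented descriptively". For the long phase: "In phase 2, mortality, hospitalizations, and exacerbations will be presented with descriptive statistics and analysed using Kaplan–Meier curves and Cox proportional hazard models".

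Table 5 marks the Feasibility row with footnote c, "not for usual care group", but puts no such mark on the Adverse events row. Under Monitoring and safety, all adverse events go to the data monitoring committee every third month.

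**The concern.** The formula is stated, so this is not a matter of detail left to the analysis plan. Both of its parts depend on attendance after randomisation. The numerator accepts an event only if it happens during a session. The denominator shrinks when a participant stops coming, and adverse events are among the listed reasons for discontinuing the intervention. The same harm can therefore score very high or zero, depending on when it appears.

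The Discussion presents supramaximal HIIT as a safe and feasible way to reach very high intensities. If HIIT and MICT differ in delayed events, such as pain or injury that shows itself after the session, the session ratio could look the same in both arms. If they differ in early leaving, the ratio could differ when the number of harmed participants does not.

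**Working it through.** The article states no expected adverse event rate, so there is no figure to reproduce. The check applies the stated formula to simple cases.

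**Inputs**
- Formula (Feasibility of interventions): rate = S / A, where S = sessions with any adverse event and A = attended sessions.
- Phase 1 training sessions (Table 1): 30 are numbered, and session 12 is replaced by the interim tests, so 30 − 1 = 29.
- The event patterns below are assumed, for illustration only.

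| Participant | S / A | Rate |
|---|---|---|
| One event in a session, attends all 29 | 1/29 | 3.4% |
| Three events in one session, attends all 29 | 1/29 | 3.4% |
| Event in session 3, then stops | 1/3 | 33.3% |
| Event in session 1, then stops | 1/1 | 100% |
| Event at home after session 3, then stops | 0/3 | 0% |
| Event at home, attends all 29 | 0/29 | 0% |
| Randomised, attends no session | 0/0 | undefined |

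The third and fifth rows carry the main point: one event that ends training after three sessions scores 33.3% or 0%, depending only on whether it arose on the bicycle. The first two rows show that number and severity do not enter. The last row shows that the rate cannot be given for everyone randomised.

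**Averaging.** The section Outcomes summarises results as mean or median, depending on distribution. Take two participants, one with 1/1 and one with 1/29. The mean of their rates is (1 + 1/29)/2 = 51.7%, while their pooled rate is (1 + 1)/(1 + 29) = 2/30 = 6.7%. A median would not repair this: if more than half of an arm has no in-session event, the median is 0% whatever happens to the rest.

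**What else covers events outside sessions**
- Phase 1: hospitalisations and exacerbations, described only. Mortality is named as an outcome for phase 2 only, and exacerbations apply to COPD only.
- Phase 2: mortality, hospitalisations and exacerbations, with Kaplan–Meier and Cox analyses.
- Both phases: dropout and non-attendance with reasons, which show such events only indirectly.

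So for HIIT versus MICT in the first 12 weeks, no defined rate covers an event outside a session. In phase 2, events outside sessions that do not lead to one of the three clinical outcomes are in the same position. Home training there is "unsupervised cycling, individual, phone call delivery every two weeks", so placing an event inside or outside a session is likely to rest on the participant's own account.

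**The case against.** The strongest reply is that the ratio is a feasibility measure and is never called the safety comparison. It sits beside documentation of occurrence and severity that is not limited to sessions, every event goes to the monitoring committee, and fuller adverse event tables commonly belong in the analysis plan, which is not shown. Much of this stands. It means that the data on HIIT and MICT should exist, and that the absence of further tables from the article is no fault. It does not change what the stated formula does, and committee reporting is oversight, not a reported comparison between arms.

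Three stronger readings are tempting, and the documents do not support them.
- A reader might infer that usual-care events are left out of any harm comparison. They are not: usual care is one of the three phase 2 arms, and mortality, hospitalisations and exacerbations have planned time-to-event analyses. That the session ratio has no value in usual care follows from its purpose.
- A reader might infer that every event that stops attendance is lost. An event during a session is counted, and its rate is raised by the short denominator. Only an event outside a session is lost.
- A reader might take the small share of clock time spent in sessions as the share of events seen. At the starting session lengths of 20 and 30 minutes, 29 sessions fill 9.7 and 14.5 of the 2,016 hours in 12 weeks, or 0.5% and 0.7%. Risk is not uniform over those hours, so these figures estimate no missed events.

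**Conclusion.** The point holds in a limited form. The only numerical comparative rate defined for adverse events in general misses events between sessions, ignores number and severity within a session, moves with early leaving (100% against 3.4% for one in-session event) and is undefined for a randomised participant with no attended session. The gap is widest in phase 1, where the other event outcomes are described without a defined rate.

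The size of any bias cannot be estimated, because the article gives no event frequencies and no split between events inside and outside sessions. The percentages above show how the formula behaves and do not forecast results. The conclusion assumes that the formula is applied as worded. It concerns safety and tolerability reporting and leaves the primary efficacy analyses untouched. If the analysis plan already tabulates all documented events by arm, only the label of the ratio remains to be settled.

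**What to change.** Keep the ratio, but call it session tolerability and confine it to HIIT versus MICT.

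For the HIIT versus MICT safety comparison, report all documented adverse events from allocation to the end of follow-up, whether or not they arose in a session. Give the number of participants with at least one event and the events per person-month, each by the four severity categories, in everyone randomised and by allocated arm. Show COPD and healthy controls separately, as in the primary analyses. The article already intends to retain participants who discontinue training where possible, so person-time can continue after training stops.

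For contrasts with usual care, rely on the planned hospitalisation, exacerbation and mortality outcomes, and on event sources common to all arms. General adverse event capture in usual care is not shown: the event content named for its telephone contact is a call "every 3 months including assessment of symptoms of exacerbations", against fortnightly calls in the training arms. A raw comparison of all events would partly measure frequency of contact.

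The cost is a change of wording and one extra table, from data on HIIT and MICT that the article already says will be documented. The reported event numbers will be higher than the session-based ones, which the text should explain.

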#### Hospitalisations

Number of hospitalisations per participant. Time, cause, length of stay, and emergency room visits (with no hospitalization afterwards) and their cause will also be extracted. Hospitalizations and emergency room visits will be classified as respiratory or non-respiratory. Data on hospitalizations will be extracted from the participant’s medical record and, when available, cross-checked with the participant’s diary (an outcome measure only in phase 2).

#### Exacerbations

Number of COPD exacerbations per participant (COPD only) during the trial period will be collected (an outcome measure only in phase 2).

